### Dose limiting toxicities

DLTs will be assessed from the first dose in cycle 1 day 1 up until cycle 1 day 28 during phase I. A haematological DLT is defined as BM aplasia/hypoplasia, defined as overall marrow cellularity less than 25% (malignant infiltration or other causes are excluded), which does not recover by cycle 1 day 28. This includes an absolute neutrophil count of less than 0.5×10^9^/L and a non-transfusion dependent platelet count of less than 25×10^9^/L due to BM aplasia/hypoplasia. In addition, grade 4 febrile neutropenia, and any grade 5 AE are also defined as a haematological DLT.

Non-haematological DLTs in group A are defined as left ventricular ejection fraction <45% as measured by echocardiogram; and in group P as >15% reduction in shortening fraction from baseline by echocardiogram. Results must be viewed by a consultant cardiologist to confirm that there has been a genuine deterioration in cardiac function. In addition, any grade 5 AE, grade 3 nausea or vomiting on or before C1D28 only which does not resolve to <grade 2 within 48 hours (with or without supportive care), grade 3 mucositis on or before C1D28 only which does not resolve to grade <2 within 48 hours (with or without supportive care), any other grade 3 or 4 non-haematological toxicity, specifically excluding: alopecia; dexamethasone related CTCAE grade 3 toxicities (eg, hyperglycaemia, muscle weakness, psychosis, avascular necrosis); tumour lysis syndrome; and increased alanine transaminase or aspartate aminotransferase.

Suspected DLTs will be reviewed and confirmed by the Trial Safety Committee (TSC) during dose decision meetings at the end of each cohort during phase I.

### Statistical analysis plan

Both groups (A and P) will be analysed separately for both phases of the trial. If the response rates in the two groups are seen to be similar in the phase II component of the trial, then there may be some consideration to analysing response in the adult and paediatric groups collectively. The phase I evaluable population includes those patients who do not withdraw/die or discontinue treatment due to non-treatment related causes before the end of the DLT assessment period. A patient is evaluable regardless of the above if they experience a DLT. The phase II evaluable population includes all patients who received any treatment. There is no scope to replace unevaluable patients in the trial.

#### Phase I

The maximum number of patients to be recruited in phase I is 24; 12 into each group in parallel.

The trial will use the CRM to find which doses to take forward to the phase II activity component of the trial for each group respectively. Each group will use a modified two-stage Bayesian CRM,^27^ recruiting patients in cohorts of two. The design incorporates rules to enable early stopping if the DLT rate at the lowest dose is unacceptably high. Patients are assigned to the starting dose level and follow the initial design (see tables 1 and 2) until the first DLT is observed. Once the first DLT is observed the CRM takes over and determines the ‘best’ dose level that the next cohort should be assigned to, based on the model-based predicted probabilities of toxicity at each possible dose. The acceptable level of toxicity (probability of a DLT) has been chosen to be 17% for each group, that is, the trial will aim to find the highest dose that coincides with this acceptable level. This value was selected based on discussion with clinicians concerning the acceptable rate of DLTs based on the chosen definition.

The stopping rule for toxicity used in the modified CRM is based on the probability of the true DLT rate at the lowest dose being >27%. If based on the observed data the probability of the true DLT rate being greater than this chosen value is >0.85 then the modified CRM will suggest that the trial should stop. The current MTD estimate is calculated after each cohort has been assessed for the full DLT assessment period and the next cohort of patients are then assigned to this MTD estimate. The final MTD estimate calculated after all 12 patients have been treated is the dose estimate to be considered to be taken forward to the phase II component.

This design works relatively well with computer simulations showing a probability for correctly selecting the right dose level of at least 0.6 when the true dose level is 0 or 1, around 0.5 when the true dose level is -1 and at least 0.6 for stopping early when all doses are truly too toxic.

Data will be reviewed at each dose decision stage by the independent TSC. The TSC will incorporate PK results into the decision process; the CRM will advise as to which doses are safe, with the PK additionally informing if there is a need for escalation/de-escalation.

#### Phase II

The phase II part of the trial will include patients from the phase I component that were dosed at the RP2D plus patients recruited into the expansion cohort. The number of phase I patients taken forward to the phase II assessment will be at least 4 in each group and the maximum number of patients to be recruited in the expansion cohort will be 9 in each group, giving a total of 13.

Based on data published by the TACL group (CR rate of 44% for second relapses and 27% for third relapses^28^) and seeing as we expect a mixture of second, third and higher relapses in paediatric patients and similar if not worse relapse rates for adult patients, we estimate the overall response rate on standard treatment to be approximately 35%.

This phase will use a Bayesian approach to investigate the true response rate in each group. A beta-binomial conjugate analysis will be used to create a posterior probability distribution of the true response rate using the observed trial data combined with a beta (1, 1) minimally informative prior. The trial design is based on the decision criteria that if there is a high probability (>0.80) that the true response rate is >35% then this will indicate that the treatment is worthy of further research. With 13 patients, this design works reasonably well with a low probability of 0.08 of incorrectly concluding that the treatment is worthy when the true response rate is only 25% and a high probability of 0.82 of correctly concluding that the treatment is worthy when the true response rate is 55%.

If the response rates are similar in both groups, then information may be borrowed across Groups A and P to provide more accuracy in determining the true response rate for both groups collectively

There are no planned subgroup or interim analyses.

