#### Phase II

The primary objective for the phase II expansion component will be to assess preliminary antileukaemic activity of the selumetinib/dexamethasone drug combination as defined by morphological response (CR, CR with incomplete platelet recovery (CRi), PR, non-response and for patients with CNS involvement only, clearance of CSF blasts) 28 days post-treatment end. Response evaluation will be undertaken with BM response at day 28, including MRD and CSF surveillance for CNS positive patients with standard cytology. A patient will be classified as having a response if they achieve CR or CRi at the day 28 assessment (with an acceptable window of day 15–35).

Secondary outcomes for the phase II component are;

The occurrence of AEs as measured by CTCAE V.4 and causality assessment.The occurrence/non-occurrence of DLTs in the trial defined assessment period.PK variables of selumetinib in combination with dexamethasone from the concentration time profile (AUC, C_max_, T_max_, t_1/2_).Difference in PK of selumetinib (ΔAUC) when selumetinib is administered as single agent and in combination with dexamethasone.MRD response in BM at 28 days.

Exploratory outcomes of the trial for both phases of the trial include exploratory pharmacodynamic (PD) biomarker studies if clinical responses are observed. These will include levels of phosphorylated ERK by flow cytometry in leukaemic cells from patients at several time points (cycle 1 day 1, cycle 1 day 4 and end of treatment visit), as well as retrospective mRNA profiling, including the apoptotic initiator Bcl-2-like protein 11 (Bcl2-L-11/BIM).^20 26^

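### The only false-positive figure given for phase II (0.08) is taken at a 25% response rate, ten points below the plan's own 35% bar, where the same rule gives 0.28 per group

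*Protocol article*

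**What the plan says.** All of the design elements are in the article's Statistical analysis plan, Phase II.

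- Sample size: "the maximum number of patients to be recruited in the expansion cohort will be 9 in each group, giving a total of 13". The other patients, at least 4 per group, come from phase I.
- Analysis: a beta-binomial posterior "using the observed trial data combined with a beta (1, 1) minimally informative prior".
- Decision: "if there is a high probability (>0.80) that the true response rate is >35% then this will indicate that the treatment is worthy", in the sense of deserving more study.
- Benchmark: "we estimate the overall response rate on standard treatment to be approximately 35" per cent, derived from published relapse data with a "CR rate of 44% for second relapses and 27% for third relapses".
- Operating characteristics: a "low probability of 0.08 of incorrectly concluding that the treatment is worthy when the true response rate is only 25" per cent, and a "high probability of 0.82 of correctly concluding that the treatment is worthy when the true response rate is 55" per cent.

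The article gives no probability of a worthy call at a true rate of 35%. The opening of the Statistical analysis plan says that groups A and P are analysed separately. The endpoint is defined under Trial outcomes, Phase II: "A patient will be classified as having a response if they achieve CR or CRi", judged at day 28.

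**The concern.** The decision rule asks whether the response rate exceeds 35%, and 35% is also what the plan expects from standard treatment. The natural point for a false-positive figure is therefore 35%: a drug that adds nothing to standard treatment. The article evaluates the error at 25% instead, calls it low, and concludes that the design works reasonably well. A drug with a 25% response rate would be clearly worse than the plan's benchmark, and 25% also lies below both published rates that the plan cites (44% and 27%). An error figure taken there says little about how often the rule would pass a drug that merely equals standard treatment.

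The outcome of this rule decides whether the combination is taken further. A reader who carries 0.08 away as the false-positive risk will put more weight on a positive result than the rule can bear.

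**Working it through.** **Inputs** (all from Statistical analysis plan, Phase II): n = 13 per group; prior Beta(1, 1); worthy if P(p > 0.35 | data) > 0.80; stated results 0.08 at 25% and 0.82 at 55%; no interim analyses.

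**Step 1: turn the posterior rule into a count.** With x responders among 13, the posterior is Beta(1 + x, 14 − x).

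| x of 13 | P(p > 0.35 given x) | Above 0.80? |
|---|---|---|
| 5 | 0.641 | no |
| 6 | 0.816 | yes |
| 7 | 0.925 | yes |

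The rule is 6 or more responders.

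**Step 2: reproduce the plan's own figures.** P(worthy | p) = P(X ≥ 6), with X ~ Binomial(13, p).

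- p = 0.25: 0.0802 (stated 0.08).
- p = 0.55: 0.8212 (stated 0.82).

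Both agree. The neighbouring cut-offs do not fit: 5 or more gives 0.206 and 0.930, and 7 or more gives 0.024 and 0.644. So the rule is identified without doubt.

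**Step 3: evaluate the same rule up to the plan's bar.**

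| True rate | P(worthy) per group |
|---|---|
| 25% | 0.080 |
| 27% | 0.110 |
| 30% | 0.165 |
| 35% | 0.284 |
| 55% | 0.821 |

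The probability rises with the true rate, so 0.284 is the largest chance of a wrong worthy call over all rates up to 35%. Ratio to the published figure: 0.2841 / 0.0802 = 3.5.

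**Step 4: two groups, as an illustration only.** If both groups sat at exactly 35% and were independent, the chance of at least one worthy call would be 1 − (1 − 0.2841)² = 1 − 0.7159² = 0.49.

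**Step 5: benchmark against endpoint.** The rates behind the 35% are labelled CR. The phase II endpoint counts CR or CRi. The article does not say whether the benchmark counts CRi, and the cited data are not available here, so no number can be attached to this.

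**The case against.** The best defence is that nothing printed is false. The 0.08 is right, and its condition stands in the same sentence. The prior, threshold and sample size are all given, so a reader can work out the value at 35%. **This stands.** A reader might infer that the plan miscalculated its error rate; it did not.

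Second, the study is a non-randomised, signal-seeking trial that claims no type I error level, and a fair chance of passing at the boundary is built into a 0.80 posterior threshold. With 13 patients the adjacent choices at 35% are 0.28 (6 or more) and 0.13 (7 or more), and the stricter one cuts the chance of a worthy call at 55% from 0.82 to 0.64. **This also stands**, as a reason to keep the rule. It is not a reason to describe the risk by its value at 25% alone.

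Third, 25% is not far from the plan's reasoning: it expects third and higher relapses, cites 27% for third relapse, and thinks adults may do no better. **This has some weight**: at 27% the chance is only 0.11. Yet the plan settles on one 35% bar for both groups and never presents 25% as the rate on standard treatment.

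Fourth, the full protocol may hold more scenarios. It may, but the article chose to publish an error figure and to call it low. The point is about that statement, not about a missing table.

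Two stronger readings are tempting. One is a trial-wide error of 0.49. The plan makes a separate decision for each group and claims no trial-wide error rate, so this is at most a secondary illustration. The other is that a benchmark without CRi makes the bar too low and the risk higher still. The documents show neither whether the benchmark leaves CRi out nor by how much, so no such figure is justified.

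**Conclusion.** The point holds as a matter of where the error is evaluated, not of arithmetic. The published false-positive figure is taken ten points below the plan's own decision bar. At the bar, which is also its estimate for standard treatment, the chance of a worthy call is 0.28 per group; over true rates from 25% to 35% it runs from 0.08 to 0.28. Calling the risk low is not supported for a drug that only matches the benchmark.

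This rests on exactly 13 evaluable patients in a group, the Beta(1, 1) prior, the 0.80 threshold, one analysis at the end, and no borrowing between groups. It does not show that the rule or the sample size is wrong: a risk of 0.28 may be acceptable in a signal-seeking trial, provided that it is stated. The CR and CRi labels raise only a question of confirmation.

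**What to change.** Replace the sentence on operating characteristics with:

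> With 13 patients per group the rule is 6 or more responders; the probability of concluding the treatment is worthy is 0.28 when the true rate equals the 35% estimate for standard treatment, 0.08 at 25% and 0.82 at 55%.

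Do not describe the false-positive risk as low without the 35% figure. If a two-group figure is wanted, give 0.49 as an illustration with its assumptions (independent groups, both at exactly 35%).

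Separately, confirm whether the 35% benchmark counts CRi. If it does not, show the posterior for CR alone beside the primary one.

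The cost is one reworded sentence, a less favourable published figure and, at most, one extra posterior per group. The rule, the threshold and the number of patients do not change.

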### PK and PD samples

Blood samples for PK and PD analysis will be obtained on days 1, 2 and 4 of cycle 1, with blood samples for PK analysis collected again on day 1 of cycle 2, and blood samples for PD analysis obtained at the end of trial treatment.

For PK analysis plasma will be subjected to liquid chromatography-mass spectrometry analysis to quantification concentrations of selumetinib, its major metabolite N-desmethyl selumetinib and dexamethasone. Two types of PD samples will be prepared from peripheral blood samples of patients who have a white cell count >10×10^9^/L; samples will either be fixed on site in BD Lyse Fix solution or collected separately in Blood RNA Preservative Tubes. These PD samples will be transferred to the UK Biobank at the University of Birmingham for storage.

All samples will be collected in accordance with national regulations and requirements including standard operating procedures for logistics and infrastructure. Samples will be taken in appropriately licensed premises, stored and transported in accordance with the Human Tissue Authority guidelines and National Health Service trust policies.

### AEs reporting and analysis

The collection and reporting of AEs as measured by CTCAE V.4 will be in accordance with the Research Governance Framework for Health and Social Care and the requirements of the National Research Ethics Service. Definitions of different types of AEs are listed in online supplemental appendix 5; this includes abnormal laboratory findings which are considered clinically significant. The reporting period for AEs will be from the date of commencement of protocol defined treatment until 28 days after the administration of the last treatment. The investigator should assess the seriousness and causality (relatedness) of all AEs experienced by the patient (this should be documented in the source data) with reference to the protocol. In addition, DLTs will be assessed for the phase I part of the trial only. All will be reported using the applicable electronic case report form (CRF).

10.1136/bmjopen-2021-059872.supp5Supplementary data

### Data management

CRFs can be entered online into the electronic Remote Data Capture system hosted by CRCTU at the University of Birmingham. Authorised staff at sites will require an individual secure login username and password to access this online data entry system. Paper CRFs must be completed, signed and dated, and returned to the SeluDex Trial Office by the investigator or an authorised member of the site research team. Data reported on each CRF should be consistent with the source data or the discrepancies should be explained. If information is not known, this must be clearly indicated on the CRF. All missing and ambiguous data will be queried. All sections are to be completed.

All trial records must be archived and securely retained for at least 25 years. No documents will be destroyed without prior approval from the sponsor, via the SeluDex Trial Office. On-site monitoring will be carried out as required following a risk assessment and as documented in the Quality Management Plan. Any monitoring activities will be reported to the central SeluDex Trial Office and any issues noted will be followed up to resolution. SeluDex will also be centrally monitored, which may trigger additional on-site monitoring. Further information regarding data management is provided in the study protocol.

The CRCTU will hold the final trial dataset and will be responsible for the controlled sharing of anonymised clinical trial data with the wider research community to maximise potential patient benefit while protecting the privacy and confidentiality of trial participants. Data anonymised in compliance with the Information Commissioners Office requirements, using a procedure based on guidelines from the Medical Research Council Methodology Hubs, will be available for sharing with researchers outside of the trials team within 12 months of the primary publication.

### Trial organisation structure

The University of Birmingham will act as sponsor to this international, multicentre study: Research Support Group, [name]. Email: [contact]. The trial is being conducted under the auspices of the CRCTU, The University of Birmingham according to their local procedures. The Trial Management Group (TMG) will be responsible for the day-to-day running and management of the trial. Members of the TMG include the chief investigator, coinvestigators, biological coordinators, trial management team leader, senior trial coordinator, trial coordinator, lead trial statistician and trial statistician. The TMG will have regular meetings during recruitment. The TSC will consist of independent clinicians, [name] and [name], as well as an independent statistician, [name].

Data analyses will be supplied in confidence to the independent TSC, which will be asked to support dose decisions and advise on whether the accumulated data from the trial, together with the results from other relevant research, justify the continuing recruitment of further patients. The TSC will operate in accordance with a trial specific charter based on the template created by the Damocles Group. The TSC will meet at the end of every cohort in phase I and at least every 6 months in phase II, or more often if required, for example, an emergency meeting may also be convened if a safety issue is identified. The TSC will report directly to both the SeluDex TMG who will convey the findings of the TSC to the funders/sponsor as appropriate or when specifically requested by these parties.

### Confidentiality

Confidential information collected during the trial will be stored in accordance with the relevant data protection legislation in each country, including the General Data Protection Regulation 2018. As specified in the PIS and with the patient’s consent, patients will be identified using only their initials, date of birth and unique trial ID number. Authorised staff may have access to the records for quality assurance and audit purposes. The Trials Office maintains the confidentiality of all patients’ data and will not disclose information by which patients may be identified to any third party other than those directly involved in the treatment of the patient and organisations for which the patient has given explicit consent for data transfer (eg, laboratory staff).

### Trial registration

ISRCTN: 92323261. Date applied: 22 January 2018; date assigned: 23 May 2018. Due to administrative delays, the date assigned occurred 5 days after the first patient was recruited (18 May 2018).

EudraCT: 2016-003904-29. Retrospective registration by UK competent authority (Medicines and Healthcare Products Regulatory Agency, MHRA): 27 March 2019.

ClinicalTrials.Gov: NCT03705507. Retrospective registration: 15 October 2018.

ITCC-063 study

### Trial status

Recruitment for the trial opened in April 2018 and the first patient was recruited on 18 May 2018; recruitment is expected to last until 31 January 2023. A list of open sites can be obtained from the SeluDex Trial Office ([contact]).

### Ethics and dissemination

The trial will be performed in accordance with the recommendations guiding physicians in biomedical research involving human subjects, adopted by the 18th World Medical Association General Assembly, Helsinki, Finland and stated in the respective participating countries laws governing human research, and Good Clinical Practice. The protocol was approved by the medical ethical committees of all the participating countries. UK ethics approval (17/YH/0123) was granted by Yorkshire and The Humber—Leeds West Research Ethics Committee on 12 July 2017. Initial UK Competent Authority approval was granted by the Medicines and Healthcare products Regulatory Agency on 5 May 2017, with subsequent protocol versions approved; current version in use is 9.0, 22 March 2021. Participants are required to provide written informed consent/assent. A meeting will be held after the end of the study to allow discussion of the main results among the collaborators before publication. Results of the primary and secondary endpoints will be disseminated through national and international presentations and submitted for publication in peer-reviewed journals. Manuscripts will be prepared by the TMG and authorship determined by mutual agreement.

